## Abstract

**Background:**

Depressive disorders are the most common form of mental disorders in community and health care settings. Unfortunately, the treatment of Major Depressive Disorder (MDD) is far from satisfactory. Vagus nerve stimulation (VNS) is a relatively new and promising physical treatment for depressive disorders. One particularly appealing element of VNS is the long-term benefit in mood regulation. However, because this intervention involves surgery, perioperative risks, and potentially significant side effects, this treatment has been limited to those patients with treatment-resistant depression who have failed medication trials and exhausted established somatic treatments for major depression, due to intolerance or lack of response.

This double-blinded randomized clinical trial aims to overcome these limitations by introducing a novel method of stimulating superficial branches of the vagus nerve on the ear to treat MDD. The rationale is that direct stimulation of the afferent nerve fibers on the ear area with afferent vagus nerve distribution should produce a similar effect as classic VNS in reducing depressive symptoms without the burden of surgical intervention.

**Design:**

One hundred twenty cases (60 males) of volunteer patients with mild and moderate depression will be randomly divided into transcutaneous vagus nerve stimulation group (tVNS) and sham tVNS group. The treatment period lasts 4 months and all clinical and physiological measurements are acquired at the beginning and the end of the treatment period.

**Discussion:**

This study has the potential to significantly extend the application of VNS treatment for MDD and other disorders (including epilepsy, bipolar disorder, and morbid obesity), resulting in direct benefit to the patients suffering from these highly prevalent disorders. In addition, the results of this double-blinded clinical trial will shed new light on our understanding of acupuncture point specificity, and development of methodologies in clinical trials of acupuncture treatment.

**Trials registration:**

Clinical Trials. ChiCTR-TRC-11001201 http://www.chictr.org/cn/

## Background

Major depressive disorder (MDD) is the fourth leading cause of disability worldwide [1], and is projected to become the second leading cause of disability worldwide by the year 2020 [2,3]. Despite the critical need, current treatments for these disorders are far from satisfactory [1,3] due to high non-response rate to treatments, high relapse rates, and frequent intolerable side effects. The etiology and pathogenesis of depression in MDD is not clear; however, it is generally believed that the cause of major depressive disorder is a combination of brain chemistry, family history, and psychosocial environment.

Vagus nerve stimulation (VNS) is a relatively new FDA-approved somatic treatment for treatment-resistant depression (TRD) that can produce significant and clinically meaningful antidepressant effects [1,4-6]. Studies also indicate that VNS may provide long-term sustained benefits [1,5,7], which is particularly compelling given the highly recurrent nature of MDD [3]. However, the involvement of surgery, perioperative risks, and potentially significant side effects have limited this treatment only to those patients who have been treated for depression in the past but have failed to respond to at least 4 prescribed medications and/or established somatic treatment options such as electroconvulsive therapy (ECT) for MDD [8].

This double-blinded randomized clinical trial aims to overcome these limitations of VNS by testing the efficacy of a novel method of transcutaneous vagus nerve stimulation (tVNS) to treat MDD. The rationale for using tVNS is that anatomical studies have shown that the ear is the only place on the surface of the human body where there is afferent vagus nerve distribution [9,10]. Thus, direct stimulation of the afferent nerve fibers on the ear should produce an effect similar to classic VNS in reducing depressive symptoms without the burden of surgical intervention [11].

Additionally, as an important branch of acupuncture, auricular acupuncture has been widely used to treat various disorders including MDD by stimulating points on the ear. Thus, we believe the results of this study will also enhance our understanding of acupuncture mechanisms, shedding new light on acupoint specificity.

## Methods and design

### Trial design

This study is a randomized, multicenter, double blind clinical trial with two treatment groups (tVNS and sham tVNS). Please see flow chart (Figure 1) for more details regarding the clinical procedures. The clinical endpoints are assessed by blinded independent observers. The central randomization system is used to assign patients to the tVNS or sham tVNS treatment groups. All procedures are performed by the Clinical Evaluation Center at the China Academy of Chinese Medical Sciences (CACMS) in Beijing. The Ethics committee of Institute of Acupuncture and Moxibustion, CACMS approved the experiment procedure.

**Figure 1 F1:**
[figure not shown]
Flow chart of the clinical trial.

### Setting

Investigators are conducting the trial in four hospitals in Beijing, China. These four hospitals are: Guang An Men Hospital, China Academy of Chinese Medical Sciences; Huguosi TCM Hospital, Beijing University of TCM; Acupuncture Hospital, China Academy of Chinese Medical Sciences.

### Blinding

As a double-blinded trial, both study physicians/investigators and patients are blinded to treatment group (tVNS versus sham tVNS). To ensure that both investigators and patients remain blinded, two carbon-impregnated silicone electrodes are fixed to one ear clamp (Figure 2). Only one of the electrodes; however, is connected to the electrical lead (wire) imbedded in the clamp in order to keep the operation of the study double blind. In the tVNS group, the upper electrode was wired to the transcutaneous electrical nerve stimulator (TENS) while in the sham tVNS group the lower electrode is inactively wired to the TENS.

**Figure 2 F2:**
[figure not shown]
**Locations and the stimulation electrodes on the auricular surface.** Red spots indicate the locations for transcutaneous auricular vagus nerve stimulation (tVNS) and blue spots indicate the locations for sham tVNS. The left figure shows the two tVNS points being in the innervation area of the auricular branch of vagus nerve (green). The right figure indicates the clip/electrode used in the study. To achieve the design of double-blind, two paired electrodes were fixed to one ear clamp. But only one of them was connected with the wire that was imbedded in the clamp in order to keep the operation of double-blind. In the tVNS group, the upper electrodes are wired to the machine while in the sham tVNS group the lower electrodes are wired.

Both the physician’s and the patient’s blindness to the mode of treatment are assessed after completion of all post-treatment measurements by asking each individual to guess the treatment modality they received given three options, “real tVNS”, “sham tVNS” or “uncertain”.

### Patients

#### Study population

Patients with mild or moderate MDD are recruited for the trial. ICD-10 Classification of Mental and Behavioral Disorders are used for diagnosis of MDD. Patients who voluntarily provide informed consent and meet inclusion/exclusion criteria are enrolled in this study. Inclusion and exclusion criteria include:

#### Inclusion criteria

1. Patient meets ICD-10 diagnosis standard: mild (2 typical + 2 other core symptoms), moderate (2 typical+3 other core symptoms).

2. Patient is 16–70 years of age

3. Patient stopped taking anti-depressive medication or other psychiatric medications 2 weeks before the intervention started.

4. Patient is educated beyond junior high school, in order to understand the scales.

5. Patient has exhibited symptoms for at least 2 months, and no longer than 2 years.

#### Exclusion criteria

1. Patients with current addiction to drugs

2. Patients with severe depression or suicidal thoughts

3. Patients with severe medical disorders

4. Patients with poor compliance

### Recruitment procedures

The investigators recruit patients with mild or moderate depressive symptoms using advertising and by sending flyers to the four hospitals involved in the study. After passing a pre-screening, potentially eligible patients provide informed consent in the presence of a study physician.

### Intervention and comparison

#### tVNS treatment

##### Location

The points for tVNS are located in the auricular concha area where there is rich vagus nerve branch distribution (Figure 2).

##### Intervention procedure

Patients take a seated position or they lay on their side. After the stimulation points are disinfected according to standard practice, ear clips are attached to the ear area (auricular concha) that will be stimulated. Stimulation parameters include: 1) density wave adjusted to 20Hz, with less than 1ms wave width; and 2) 1mA current turned on. The intensity is adjusted based on the tolerance of the patient. Each treatment lasts for 30 minutes and is carried on twice a day, 5 days per week for the duration of the treatment period (12 weeks).

#### Sham tVNS treatment

##### Location

The stimulation points for sham tVNS are located at the superior scapha (outer ear margin midpoint), where there is no vagus nerve distribution (Figure 2).

##### Intervention procedure

All procedures performed in the sham tVNS treatment group are identical to the procedures for the verum tVNS group.

### Choice of endpoints

All endpoints are measured at week 0 and week 10. The endpoints include the 24-item Hamilton Depression Rating Scale (HAM-D-24), the 17-item Hamilton Depression Rating Scale (HAM-D-17), Self-rating Anxiety Scale (SAS), Self-rating Depression Scale (SDS), electrocardiogram rate, breathing rate, and skin conduction response. Similar to previous studies [12,13], the primary outcome is the categorical classification of treatment response. We are interested in comparing the difference in treatment response rate between the two groups as measured by HAM-D-24, where treatment response is defined as a 50% or greater reduction in HAM-D-24 scores following a 10-week treatment.

In addition, previous studies [14-17] suggest that expectations for symptom relief can significantly influence the response to medications, acupuncture, and placebo. Thus, before the first treatment, patients are asked to rate on a scale how much they expect the treatment will relieve their symptoms, from “complete relief” to “do not work at all”.

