### Sample size calculation and statistical analysis

#### Sample size

We present here our power analysis for the primary outcome only. Since this is a novel therapy, we used the data from a previous non-controlled pilot study on treatment-resistant MDD in senior patients [18] to calculate the power. The primary outcome measure is the categorical classification of response; we define the treatment response as a 50% or greater reduction in HAM-D-24 scores following treatments. From a previous proof of concept study [18], the response rate in the tVNS group is 39%; assuming a 20% dropout rate, with 60 patient in each group, we will have 80% power to detect a difference of 25% or greater in response rate between the tVNS and the sham tVNS group based on a chi square test at a 0.05 significance level.

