#### Statistical analysis

In this study, the primary outcome measure is the categorical classification of treatment response. We define the treatment response as a 50% or greater reduction in HAM-D-24 scores following treatments. Response rates across the two groups will be compared with the chi square (*x*^2^) test.

Additionally, we will also use the HAM-D-24 score as continuous variable and apply a regression model to compare the different between two treatment groups. More specifically, in the model, the dependent variable is post-treatment HAM-D-24 score, the independent variable is treatment mode (tVNS versus sham tVNS), and covariances will include pre-treatment HAM score, age and gender. Similar analyses will also be performed in other clinical and physiological outcome measurements.

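### The protocol gives three lengths for one treatment period (4 months, 12 weeks, 10 weeks), so it is unclear whether the week-10 primary response is an end-of-treatment or a mid-treatment result

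*Protocol article*

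**What the plan says.** The protocol article states the length of treatment in three places.

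- **Abstract, Design:** "The treatment period lasts 4 months and all clinical and physiological measurements are acquired at the beginning and the end of the treatment period".
- **Intervention procedure (tVNS):** 30-minute sessions twice a day, "5 days per week for the duration of the treatment period (12 weeks". The sham arm follows suit: "All procedures performed in the sham tVNS treatment group are identical to the procedures for the verum tVNS group", so this course length covers both arms.
- **Choice of endpoints:** the assessment schedule reads "All endpoints are measured at week 0 and week 10", and for the primary outcome, "treatment response is defined as a 50% or greater reduction in HAM-D-24 scores following a 10-week treatment".

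Two later sections restate the primary outcome without a week. Sample size has "we define the treatment response as a 50% or greater reduction in HAM-D-24 scores following treatments" and Statistical analysis has "We define the treatment response as a 50% or greater reduction in HAM-D-24 scores following treatments". The supporting regression likewise takes the HAM-D-24 score after treatment as its dependent variable and names no week.

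The Blinding section places the treatment guess after all measurements that follow treatment are complete. Trial status reports 49 participants recruited when the article was submitted.

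**The concern.** The primary outcome classifies each patient as a responder or not from the change in HAM-D-24 between baseline and one later assessment. Its meaning depends on where that assessment falls in the course of treatment. Choice of endpoints is consistent within itself, since week 10 follows a ten-week course. It conflicts with the two other statements of duration. If treatment runs 12 weeks or 4 months, the week-10 score is taken part-way through, although the analysis section treats it as a score after treatment and the Abstract promises measurement at the end.

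What is at stake is interpretation. A response rate at the end of a completed course and one taken during an unfinished course answer different questions, and a reader of the results could not tell from this text which was estimated. The blinding guess inherits the ambiguity: if a longer course applies and the guess follows directly on the week-10 measurements, it too would be collected while patients are still being stimulated.

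**Working it through.** **1. The plan's own figure.** Inputs from Sample size: 60 per group, 20% dropout, 39% response on tVNS, a 25-point difference, chi-square test at 0.05. I assume a two-sided test, since sidedness is not stated, and a sham rate of 39% − 25% = 14%.

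- Evaluable per group: 60 × (1 − 0.20) = 48.
- Pooled rate: (0.39 + 0.14)/2 = 0.265.
- Standard error under no difference: √(2 × 0.265 × 0.735/48) = 0.0901.
- Standard error under the alternative: √((0.39 × 0.61 + 0.14 × 0.86)/48) = 0.0864.
- Power = Φ((0.25 − 1.96 × 0.0901)/0.0864) = Φ(0.85) = 80.2%.

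The stated 80% is reproduced. No term in the formula depends on treatment duration, and the article does not tie the 39% to any duration.

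**2. Length of each stated course.** Four months is 4 × 4 = 16 weeks if a month is counted as four weeks, or 4 × 365.25/12/7 = 17.4 weeks by the calendar. The article does not say which, so I carry the range. On neither count does 4 months come to 10 or 12 weeks.

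**3. Planned sessions.** Two a day on 5 days a week is 10 sessions a week.

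| Section | Course | Sessions | Share delivered by week 10 | Weeks left after week 10 |
|---|---|---|---|---|
| Choice of endpoints | 10 weeks | 100 | 100/100 = 100% | 0 |
| Intervention procedure | 12 weeks | 120 | 100/120 = 83% | 2 |
| Abstract, Design | 16 to 17.4 weeks | 160 to 174 | 100/174 = 57% to 100/160 = 63% | 6 to 7.4 |

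**4. Can the statements be reconciled from the text?** Week 10 would be compatible with a longer course if it were described as an interim visit with a later one to follow. No section does so, and Choice of endpoints limits all endpoints to weeks 0 and 10. The Abstract rules out a mid-course measurement by placing all measurements at the beginning and end. Setting the Abstract aside as loose wording still leaves 12 weeks against 10 within the methods. Sample size and Statistical analysis name no week, so they cannot decide the matter.

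**5. Between-arm balance.** Sham procedures are stated to be identical to active ones, so at any common week both arms have the same planned number of sessions. The randomised comparison at week 10 is not biased by this inconsistency.

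**The case against.** The strongest reply is that the primary time point is in fact named. Choice of endpoints is the only section that attaches a week to an assessment, and it gives the same figure in the schedule and in the responder definition. The sample-size and analysis sections do not contradict it. That much stands: week 10 is the named week, and the firm contradiction is about the length of treatment. It does not dispose of the point, because the definition rests on a ten-week course that two other sections deny.

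A second reply is that the full protocol, the analysis plan or the flow chart in Figure 1, none of which is shown, may settle the schedule. They may show what was intended. But the point is not that something is missing: statements in this document cannot all be true.

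A reader might also infer more than the text supports:

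- *Three rival primary time points, open to choice once data are seen.* Choice of endpoints schedules one post-baseline assessment only, so under that section there is no second score to choose from.
- *The four hospitals follow different schedules.* Nothing in the article shows or suggests it.
- *The 49 recruited patients were enrolled under contradictory instructions.* Trial status says only that they had been recruited by submission. The working protocol they were treated under is not shown.
- *The power or the between-arm test is undermined.* The power is reproduced and does not involve duration, and planned exposure is equal in both arms. The session percentages describe how far through the course week 10 falls; they do not measure bias.
- *A visit window is missing.* That is ordinary detail for the full protocol or analysis plan.

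**Conclusion.** The concern holds as an internal contradiction that reaches the definition of the primary endpoint. The article gives 4 months, 12 weeks and 10 weeks for one treatment period, and nothing shown reconciles them. If either longer course governs, the week-10 HAM-D-24 score is taken after about 83% of a 12-week course, or about 57% to 63% of a 4-month course. It is then not the end-of-treatment response the Abstract describes. If the ten-week course governs, the endpoint is coherent and the other two sections are wrong. The document does not show which was intended.

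Confidence in the contradiction is high. The percentages assume the stated twice-daily, 5-day schedule throughout and, for 4 months, a month of between four weeks and one calendar month. That the blinding guess falls during treatment is conditional on a longer course and on the guess coming soon after week 10. Correction is needed because the trial cannot say what its primary response rate measures until the sections agree.

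**What to change.** Reconcile the Abstract, the Intervention procedure and Choice of endpoints to one treatment duration; which one is for the investigators to decide. Name one primary assessment week and state whether it is the end of treatment. Use that same wording in Choice of endpoints, Sample size and Statistical analysis, so that the responder definition and the regression refer to the same score. State where the blinding guess falls relative to the last session. Make these changes before any unblinded look at the data.

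Because recruitment had begun, list for each enrolled patient the actual treatment duration and the date of the HAM-D-24 assessment, so that any departure from the reconciled schedule is visible.

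The cost is a text amendment and a listing of treatment and assessment dates. The sample size does not change.

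### A pre-treatment expectation rating is collected because expectation may influence response, but the named regression covariates omit it and no stated analysis uses it

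*Protocol article*

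**What the plan says.** Under Choice of endpoints, the protocol article reports that earlier studies suggest that "expectations for symptom relief can significantly influence the response to medications, acupuncture, and placebo". It gives this as the reason for a rating taken before the first treatment, in which "patients are asked to rate on a scale how much they expect the treatment will relieve their symptoms".

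Under Statistical analysis, the primary comparison is unadjusted: "Response rates across the two groups will be compared with the chi square" test. A secondary regression takes the post-treatment HAM-D-24 score as the dependent variable and treatment as the independent variable, and "covariances will include pre-treatment HAM score, age and gender". The section closes with "Similar analyses will also be performed in other clinical and physiological outcome measurements". The expectation rating is not mentioned there or anywhere later in the article.

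**The concern.** The article gives a reason to think that one particular baseline variable bears on outcome, and collects it for that reason. When it names the covariates of its regression, it lists age and gender, for which it offers no such reason, and leaves expectation out.

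Expectation is rated before treatment starts and patients are blinded, so allocation should not affect the rating and adjusting for it is legitimate. The setting makes it relevant: the comparator is a sham device, the main outcome is a rated symptom scale, and SAS and SDS are self-rated.

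Two things are at stake, both modest. The first is some precision in the adjusted analyses. The second is discretion: if the role of the rating is not fixed in advance, adding or dropping it after the results are seen becomes an analyst's choice.

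**Working it through.** **Inputs from the Sample size section.** The pilot figure: "the response rate in the tVNS group is 39" per cent. Size and attrition: "assuming a 20% dropout rate, with 60 patient in each group". The claim built on these inputs: "we will have 80% power to detect a difference of 25% or greater in response rate", using a chi-square test at 0.05. A 25-point difference below 39% implies 14% on sham. Evaluable patients per arm: 60 × (1 − 0.20) = 48. The article does not state whether the test is one- or two-sided; two-sided reproduces its figure.

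**Input not in the documents.** The strength of association between expectation and outcome. It is assumed below and shown as a range.

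**Step 1: the plan's own power.** Mean proportion p̄ = (0.39 + 0.14)/2 = 0.265.
- SE under the null = √(2 × 0.265 × 0.735/48) = 0.0901
- SE under the alternative = √((0.39 × 0.61 + 0.14 × 0.86)/48) = 0.0864
- Power = Φ((0.25 − 1.96 × 0.0901)/0.0864) = Φ(0.850) = 80.2%

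The stated 80% reproduces. It does not depend on expectation.

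**Step 2: does leaving expectation out harm the primary test?** A simulation with no treatment effect, 48 per arm, about 29% responding and a strong omitted prognostic factor (0.8 on the log-odds scale per SD) gave a chi-square type I error of 5.3%, close to nominal.

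**Step 3: size of a chance imbalance.** The SD of the difference in standardised means is √(2/48) = 0.204, and 1.96 × 0.204 = 0.40. An imbalance of 0.4 SD or more in either direction therefore has about a 5% probability. Its effect on the response difference is about 0.4 × √R² × φ, where φ = 0.327 is the normal density at the 26.5% point:
- R² = 0.04: 0.4 × 0.20 × 0.327 = 2.6 percentage points
- R² = 0.10: 0.4 × 0.316 × 0.327 = 4.1 percentage points

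The planned difference is 25 points.

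**Step 4: gain in the linear regression.** Adding a covariate with partial correlation r, given the other covariates, multiplies the residual variance by (1 − r²). The article gives no power for this regression, so 80% serves as the reference. Power becomes Φ((1.960 + 0.842)/√(1 − r²) − 1.960).

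| Assumed r | 1 − r² | Power |
|---|---|---|
| 0.1 | 0.99 | 80.4% |
| 0.2 | 0.96 | 81.6% |
| 0.3 | 0.91 | 83.6% |
| 0.4 | 0.84 | 86.4% |
| 0.5 | 0.75 | 89.9% |

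**Step 5: gain for response.** Response was simulated from a latent normal variable (48 per arm, 39% v 14%). Logistic tests without and with expectation were compared, so that the type of test stays the same.

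| Assumed latent R² | Unadjusted | Adjusted |
|---|---|---|
| 0.01 | about 82% | about 82% |
| 0.04 | about 82% | about 83% |
| 0.10 | about 82% | about 83% |
| 0.20 | about 82% | about 86% |

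Monte Carlo error is about 0.5 points with 6,000 runs. The chi-square test itself gave about 81% in such simulations. Setting it against an adjusted logistic model (about 84% in one run at R² = 0.10) mixes the effect of the covariate with the effect of changing the test.

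**The case against.** The strongest reply is that this is a condensed article. How an auxiliary baseline measure is used is commonly settled in the full protocol or the SAP, neither of which is shown. The article never says that expectation will be an adjustment variable, and its covariate sentence does not say that the list is complete. Baseline score, age and gender are also a defensible short set.

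Much of this stands. It limits the claim to what the article states: a reader cannot infer that expectation is absent from every analysis of the trial. It does not remove the point, because the article does name the covariates of a specific model, and the one baseline variable it gives a reason for is not among them.

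Three stronger readings are tempting, and the documents do not support them.
- *Expectation is an established prognostic factor here.* The article says only that earlier studies suggest that it can matter. It gives no strength of association, and none for this population or device.
- *Chance imbalance in expectation is a serious rival explanation for a positive result.* Randomisation is central and patients are blinded, so imbalance arises only by chance, and the 5% error rate already allows for that. If a 0.4 SD imbalance did occur with no treatment effect, the chi-square test would reject about 7% of the time at R² = 0.10 and 8.5% at R² = 0.20. That is a reason for a supportive adjusted analysis, but a shift of about 4 points at R² = 0.10 cannot by itself explain a 25-point difference.
- *The trial loses material power.* The primary test meets its stated power without the covariate.

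**Conclusion.** The point holds as a minor one. The article collects the rating for a stated reason and then omits it from the covariates that it names. The omission neither biases the treatment comparison nor invalidates the primary analysis, and no stated figure changes.

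The benefit of adding it depends on an association that the documents do not quantify: about 0.4 to 10 power points in the linear regression over the assumed range of r, and roughly 0 to 4 points for response over the assumed range of R². At the weak end of either range the gain is negligible. The firmer reason to act is that the role of the rating would be settled before anyone sees results by arm.

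**What to change.** Before unblinding, prespecify the expectation score as an additional covariate in the secondary HAM-D-24 regression and in the similar models for the other outcomes, and state how it is coded (ordered or continuous). Optionally, add one supportive expectation-adjusted analysis of response. Label any treatment-by-expectation analysis as exploratory, since an interaction will have low power with 48 evaluable patients per arm. Leave the primary chi-square test and the sample size unchanged.

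The cost is a sentence or two in the SAP and one degree of freedom per model if the score is entered as continuous. The rating is already part of the baseline assessment, so no new data are needed. The article's Trial status section reports 49 recruited at submission, of the 120 planned.
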